#### 2.4.2. Round Two

Themes originating from the open-ended responses and analysis of data from the structured questions of round one will guide the formation of the round two questionnaire. In round two, participants can modify their answers from round one based on results and feedback from that round. Participants will be able to see the amount of consensus on statements from the previous round, and where they answered compared to the group. Participants will not need to vote further on items achieving consensus in this round, and therefore items achieving consensus will not be included in the round three questionnaire. Items achieving 75% agreement or more for “disagree” or “strongly disagree” will be removed. Items that received an overall rating of “unsure” or that were rated as “strongly agree” or “agree” by less than or equal to 50% of participants during the first and second round will require further investigation by steering committee and items/questions will be amended for the next round. A table will be created to provide explanations for amended items moving into round three.

#### 2.4.3. Round Three

In round three, participants can modify their answers from round two based on results and feedback from that round. Participants will be able to see the amount of consensus on statements from the previous round, and where they answered compared to the group. If consensus is still not reached on a particular item, items will be reviewed and revised according to the criteria by the PI and steering committee and a fourth round will be performed. If all items have reached consensus according to our methods after round three, the questionnaire process will be complete. However, a fourth round may be performed to investigate expert agreement on an official list of recommendations for DN in headache management comprising all consensual items.

### 2.5. Statistical Analysis

Standard descriptive statistics will be used to describe the demographic characteristics of participants based on the first group of questions of the round one questionnaire. Anonymous answers from the open-ended questions following round one will be analyzed thematically as described in the study procedures section of this protocol. Percentage agreement calculations will be the primary measure throughout all rounds of this Delphi study [90]. However, depending on the data, measures of dispersion and central tendency may be used in place of or in addition to percentage agreement, using Interquartile Range (IQR) and/or Median, respectively, as these measures are also widely used in Delphi studies to define consensus [68]. Data will be analyzed using SPSS 30.0.0 or other statistical software at the end of each round. Wilcoxon rank-sum tests will be used for the final round to evaluate stability and consistency of responses between the final two rounds, with the aim of moving toward consensus [68]. The response rates of participants will also be measured following each round, which is increasingly investigated in Delphi studies [60,62].

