## Abstract

**Background**: Dry needling is increasingly utilized by clinicians in the treatment of patients with headaches. Although current evidence supports the use of dry needling for reducing headache pain, needling approaches are inconsistent among published studies, and no guidelines on dry needling for headaches have been established. **Methods**: A study will be conducted using the Delphi method, consisting of three rounds of questionnaires sent to an expert panel of clinicians and researchers. **Results**: To guide the development of the initial survey, we completed a literature review of articles related to dry needling for headaches. A steering committee will assess the initial survey items synthesized from the literature search and provide recommendations for the first and subsequent rounds of the study. Percentage agreement will be the primary measure throughout all rounds of this study. We define consensus to have been reached when 75% agreement is achieved. **Conclusions**: We seek to develop clinical recommendations that will guide research and treatment practices regarding dry needling for headaches. Having consensus-driven recommendations on dry needling for headaches will assist researchers in the design of future studies on this condition. In addition, having guidelines that clinicians can reference prior to the delivery of dry needling for headaches would benefit patient care.

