Experts will rate their level of agreement for the included items using a 5-point Likert-scale, except for the initial open questions that will be included as part of the first round. Answers to open questions will be analyzed by the Principal Investigator (PI) and steering committee and converted to closed questions for the next survey round. After each item and open-ended question, there will be space for expert comments. Participant responses from the open-ended questions will be coded alongside each other and analyzed to identify concepts, categories and themes [88]. The PI will organize the data into a Microsoft Excel table and present it to the steering committee. An iterative process will ensue to determine what additional closed question items can be created for round two of the questionnaire based on the thematic analysis. Following the final round of the study, data from REDCap will be exported for statistical analysis.

We define that consensus has been reached when 75% percent of participants “strongly agree” or “agree” with an item. A percentage agreement value of 75% is commonly chosen for determining consensus among Delphi studies, according to a recent review [89]. Participants will not need to vote further on items achieving consensus in round one, and therefore items achieving consensus will not be included in the round two questionnaire. Items achieving 75% agreement or more for “disagree” or “strongly disagree” will be removed. Items that received an overall rating of “unsure” or that were rated as “strongly agree” or agree” by less than or equal to 50% of participants during the first and second round will require further investigation by the steering committee and items/questions will be amended for the next round. That is, if items that are believed to be important fall just below the threshold for consensus, the PI and steering committee will consider including these items as posteriori considerations provided that sufficient justification is provided. A table will be created to provide explanations for amended items moving into the next round. Following each round, the steering committee will review all questionnaire data, participant responses and comments, and the PI will make edits accordingly to prepare for the next survey round.

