## 3. Results

We plan to present our results through high-impact publication for the benefit of healthcare professionals, researchers, and patients. Outcomes will be displayed quantitatively (i.e., percentage agreement calculations, and possibly IQR and Median) and qualitatively. At the time of submission of this Delphi study protocol, the first round of this study is planned to begin on or before 1 March 2025.

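### Section 2.5 allows the 75% consensus criterion to be replaced by IQR or median after the votes are seen, with no trigger and no cut-off

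*Protocol article*

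**What the plan says.** Consensus is defined in two places. The Abstract states "We define consensus to have been reached when 75% agreement is achieved". Section 2.4.1 states "We define that consensus has been reached when 75% percent of participants" choose one of the two agreeing categories of the 5-point scale. Section 2.5 confirms the role of this measure: "Percentage agreement calculations will be the primary measure throughout all rounds of this Delphi study".

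The sentence that follows in section 2.5 reads, in part, "depending on the data, measures of dispersion and central tendency may be used in place of or in addition to percentage agreement". It names the IQR and/or the median, and gives as the reason "as these measures are also widely used in Delphi studies to define consensus". On timing, the same section says "Data will be analyzed using SPSS 30.0.0 or other statistical software at the end of each round". Section 3 describes the planned output as "percentage agreement calculations, and possibly IQR and Median".

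**The concern.** A measure cannot be primary in all rounds and also be replaceable according to what the data show. The reason given for the substitutes is that they define consensus, so their intended role goes beyond describing the spread of votes.

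Consensus status is the outcome that drives this study. Under sections 2.4.1 and 2.4.2 an item that reaches consensus leaves the voting. Under section 2.4.3 the items with consensus make up the list of recommendations. If the criterion can be picked after a round's votes are tabulated, the threshold fixed in advance no longer guards against choosing the rule that gives the preferred list. A switch after round one or two would also change which items the panel sees again, and later analysis cannot undo that.

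**Working it through.** **Inputs from the article.** Panel of 30 (section 2.2); 5-point scale, scored here 1 to 5 with 3 = unsure, 4 = agree and 5 = strongly agree (section 2.4.1); threshold 75% (Abstract, section 2.4.1). The 75% is a convention taken from the Delphi literature, so there is no derived figure to reproduce.

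**Assumed inputs.** The article gives no cut-off for the substitutes. I use median ≥ 4 and IQR ≤ 1 as one illustration and IQR = 0 as a stricter one.

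**Step 1: the stated rule.** 0.75 × 30 = 22.5, so 23 experts must agree. 23/30 = 76.7%; 22/30 = 73.3% fails.

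**Step 2: two items under the assumed rule.** Quartiles use linear interpolation: with 30 ordered votes, Q1 lies at position 29 × 0.25 + 1 = 8.25, the median midway between votes 15 and 16, and Q3 at 29 × 0.75 + 1 = 22.75.

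| Votes | Agreement | Q1 | Median | Q3 | IQR | 75% rule | Median ≥ 4 and IQR ≤ 1 |
|---|---|---|---|---|---|---|---|
| 13 unsure, 17 agree | 17/30 = 56.7% | 3 | 4 | 4 | 1 | fails by 18.3 points | met |
| 14 unsure, 16 agree | 16/30 = 53.3% | 3 | 4 | 4 | 1 | fails by 21.7 points | met |

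**Step 3: the smallest number agreeing that can satisfy each rule.** This comes from enumerating every possible distribution of 30 votes, under linear interpolation and under the (n + 1)p quartile definition. Both give the same minima.

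| Rule | Minimum agreeing |
|---|---|
| ≥ 75% agreement | 23/30 (76.7%) |
| Median ≥ 4 and IQR ≤ 1 | 16/30 (53.3%) |
| Median ≥ 4 alone | 15/30 (50%) |
| IQR ≤ 1 alone | 0/30 |

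The last row arises because the IQR measures spread and not direction: a panel that is unanimously unsure has an IQR of 0. Under the combined rule, items with 16 to 22 agreeing (53.3% to 73.3%) could change status according to the measure chosen.

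**Step 4: the other direction.** Take median ≥ 4 and IQR = 0 with linear interpolation. Q1 and Q3 can be equal only if votes 8 and 9 are equal, so vote 8 is already at least 4 and at least 30 − 7 = 23 experts agree. Every such item also meets 75%. The switch can also tighten the rule: 7 unsure, 1 agree and 22 strongly agree is 23/30 = 76.7%, but by the (n + 1)p definition Q1 sits at 31 × 0.25 = 7.75, giving 3 + 0.75 × (4 − 3) = 3.75. With Q3 = 5 the IQR is 1.25, which fails IQR ≤ 1.

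**Step 5: how often it could matter.** Suppose experts vote independently and each agrees with probability p. Then P(X ≥ k) = Σ C(30, j) pʲ(1 − p)³⁰⁻ʲ, summed over j = k to 30.

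| p | P(≥ 23 agree) | P(≥ 16 agree) |
|---|---|---|
| 0.50 | 0.003 | 0.428 |
| 0.60 | 0.044 | 0.825 |
| 0.70 | 0.281 | 0.983 |
| 0.80 | 0.761 | 1.000 |

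The right-hand column is an upper bound for the combined median and IQR rule, since 16 agreeing is necessary but does not always suffice.

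**The case against.** The best case for the plan is that the clause is permissive and sits beside a clear declaration that percentage agreement is primary. Every operational rule (consensus, removal, amendment) is written in percentages. Section 3 lists percentages as the planned output and treats IQR and median as optional, so a reader could check any recommended item against 75%. This limits the harm if percentages are published for every item. It does not remove the permission to decide consensus by another measure, or its effect on which items return to the panel.

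Three further points have some force. Consensus is not the only thing measured: stability between rounds, response rates and thematic analysis are also planned. It is still the outcome that determines the recommendations. A journal article may leave an exact IQR cut-off to a fuller document, so the missing cut-off would carry little weight alone; the fault is the stated permission to replace. And step 4 shows that a strict substitute would not loosen the criterion, so the gap in step 2 is one scenario.

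The condition about the data could also be read as referring to the form of the responses and not to how the votes fell. Since the rated items all share one 5-point scale, that reading is the less likely one, and the text does not state it.

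**Conclusion.** The point holds and should be corrected. Section 2.5 contradicts the fixed definition in the Abstract and section 2.4.1 by letting the criterion that generates the recommendations be replaced after the votes are known. That conclusion rests on the wording alone.

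Its size depends on a cut-off the article does not give. With 30 responders, median ≥ 4 and IQR ≤ 1 could lower the agreement needed from 76.7% to 53.3%; IQR = 0 with median ≥ 4 would not lower it; and an item at 76.7% can fail IQR ≤ 1 under one quartile definition. The probabilities in step 5 also assume independent votes with a common p. Reporting median and IQR in addition to percentage agreement is harmless provided they are descriptive.

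**What to change.** In section 2.5, delete the words that permit replacement. State that at least 75% agreement is the sole consensus criterion in every round, and that median and IQR are reported for every item as descriptive statistics that cannot change its consensus status. If the investigators do want dispersion or central tendency to count, the alternative is to fix a combined rule before any votes are examined, giving cut-offs, quartile definition and what happens when the measures disagree.

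Section 2.4.1 separately lets the committee consider important items that fall just short of the threshold. For 75% to be decisive, such items should be labelled as not having reached consensus and listed apart.

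The cost is one sentence in section 2.5, one clarifying line in section 2.4.1, and a matching entry in the registration if it carries the same wording (it is not shown). No extra data are needed. If round one has already run, the change should be dated and should say whether results had been seen.

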There are no official guidelines available for researchers to use when selecting experts for a Delphi study, or determining appropriate sample size [68]. Based on a systematic review of the Delphi literature, Junger et al. confirmed that, at a minimum, the criteria used for the selection and recruitment of experts should be explained in the methodology, along with survey response rates and information related to the participants expertise [61]. For this study, we will lean on clinical and academic experience/knowledge related to headache and dry needling, along with authorship of peer-reviewed publications, which are commonly used criteria to define expertise in Delphi studies [68]. We aim to recruit and retain 30 experts from multiple countries, which is similar to the number of participants included in previous Delphi studies on the topic of headache [18,40] and DN [65]. Moreover, selecting an expert panel size larger than 30 may not improve the Delphi results and potentially contributes to lower survey response rates [69]. Importantly, a homogenous group of 30 experts with specialized knowledge and experience, in our case DN for headaches (CGH, TTH and migraine), is sufficient to obtain stable results from a Delphi survey [70]. Thirty participants that best represent the expert population most appropriate for this study will be chosen, following agreement to participate.

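### Stability between the final two rounds is assessed only with a test of difference and no tolerated change, so with about 30 experts a non-significant result would not show that an unamended item was stable

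*Protocol article*

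**What the plan says.** Section 2.5 (Statistical Analysis) assigns the stability question to one procedure: "Wilcoxon rank-sum tests will be used for the final round to evaluate stability and consistency of responses between the final two rounds". It adds that the aim is to move toward consensus. It states no significance level, no tolerated change and no rule for reading the result.

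The rest of the design sets the context:

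- Panel size (2.2): "We aim to recruit and retain 30 experts from multiple countries".
- Scale (2.4.1): "Experts will rate their level of agreement for the included items using a 5-point Likert-scale".
- Consensus (2.4.1): "We define that consensus has been reached when 75% percent of participants “strongly agree” or “agree” with an item".
- Before round three (2.4.2): "items achieving consensus will not be included in the round three questionnaire". Items with agreement at or below 50%, or rated unsure overall, are amended.
- Round three (2.4.3): "In round three, participants can modify their answers from round two based on results and feedback from that round". The same experts therefore answer both rounds, having seen the group result and their own position.

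**The concern.** To call an item stable is to claim that responses did not change by a relevant amount. A test of difference cannot establish that. With no tolerated change stated, the only result that could be taken to support stability is a non-significant one, and in a small panel this may mean only that the test could not see the change.

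The carry-over rules make this matter. If round three is the last round, an unamended item that reaches consensus there must have been below 75% in round two and at or above 75% in round three. It has therefore moved, after group feedback, between the two rounds being compared. Such an item could be reported both as consensual and as stable. Attrition makes a non-significant result easier still to obtain.

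**Working it through.** The article gives no power, significance level or margin for this test, so there is no figure of its own to reproduce.

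**Inputs.** From the article: 30 experts, a 5-point scale, consensus at 75%. Since 22/30 = 73.3% and 23/30 = 76.7%, consensus needs 23 experts. Assumed: two-sided 5% level; round-two ratings of 6 strongly agree, 12 agree, 7 unsure, 5 disagree (18/30 = 60%).

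**Which moves are possible.** Agreement of 50% or less triggers amendment and 75% or more removes the item. With 30 answering, an unamended carried-over item starts between 16/30 and 22/30.

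**Example: 18/30 to 23/30.** Seven experts move from unsure to agree and two from agree to unsure. Round three is then 6, 17, 2, 5.

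*Rank-sum test.*
- U = 6×27 + 17×18 + 2×8.5 + 5×2.5 = 497.5; expected value 30×30/2 = 450.
- Pooled ties are 12, 29, 9 and 10, so Σ(t³−t) = 1,716 + 24,360 + 720 + 990 = 27,786.
- Variance = (900/12)×[61 − 27,786/(60×59)] = 3,986; SD = 63.1.
- z = 47.5/63.1 = 0.75, **p = 0.45**.

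*Signed-rank test on the same moves.* All nine changes are one category, so z = (7−2)/√9 = 1.67, **p = 0.10** (exact 0.18).

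*Paired change.* +5/30 = +16.7 points. SE = √(9 − 25/30)/30 = 9.5 points; Wald 95% CI about −2 to +35. These data do not support a claim of no relevant change.

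**Same margins, one-way movement.** With 5 up and none down, the rank-sum p is again 0.45, because the test sees only the two margins. The signed-rank p is 0.025 asymptotically and 0.0625 exactly.

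**Other starting points.** If all answers fall in two adjacent categories, rank-sum p for a move to 23/30 is:

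| From | p |
|---|---|
| 22 | 0.77 |
| 20 | 0.39 |
| 18 | 0.17 |
| 17 | 0.10 |
| 16 | 0.06 |

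**How often a true shift is missed.** Simulation of a true move from 60% to 75% agreement, 30 experts, latent normal ratings cut into five categories; results vary by a few points between runs. The rank-sum test misses it 68% to 82% of the time over within-expert correlations 0 to 0.9. The signed-rank test misses it:

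| Correlation | Signed-rank miss rate |
|---|---|
| 0 | about 70% |
| 0.5 | about 51% |
| 0.7 | about 32% |
| 0.8 | about 20% |
| 0.9 | about 6% |

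**Is a formal rule attainable?** Under the same model with no true change, requiring the Wald CI for the paired change to lie within ±15 points labels an item stable in 0% of runs at correlation 0, about 1% at 0.5, about 5% at 0.7, about 15% at 0.8 and 36% at 0.9. Two up and none down already fails: 6.7 + 1.96×√(2 − 4/30)/30×100 = 15.6 points.

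**The case against.** **The rule is inferred.** A reader might take section 2.5 to say that p > 0.05 means stable. It does not; it attaches no label to any result. A condensed article may also leave a margin to a fuller document. Both points stand, so the absence of a margin is not itself the defect. What remains is a choice that the article does state: a difference test is the only tool named for stability.

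**Nothing else depends on it.** A reader might infer that the test alters which items become recommendations. The documents do not support that. Consensus, removal and amendment follow percentage rules, a further round depends on consensus not being reached, and percentage agreement is the primary measure. A move from 60% to 77% would be visible there. This stands and limits the point to the stability statement.

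**The scope is narrow.** Items dropped after rounds one or two, and items reworded between rounds, have no comparison to make. If non-consensual items go to a fourth round, they are first reviewed and revised, which narrows it further. This stands.

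**Much of the miss rate comes from the unpaired test.** A reader might blame all of the 68% to 82% on the missing margin. That would be wrong: experts see and revise their own answers, so high correlation is plausible, and there a signed-rank test misses far less. The logical gap survives, since a non-significant paired test does not show absence of relevant change.

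**Conclusion.** The point holds in limited form. Section 2.5 evaluates stability only with a test of difference and no tolerated change. With 30 experts, a move that creates consensus can leave that test far from significance (p = 0.45 for 18/30 to 23/30), and the paired test can also be non-significant when movement is mixed (p = 0.10 with 7 up and 2 down). Pairing reduces the problem considerably at high correlation without removing it.

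The consequence is confined to what the study may say about stability of unamended carried-over items. It does not change which items are declared consensual. The sizes rest on a two-sided 5% level, the illustrative rating distributions, the latent normal model and an unknown within-expert correlation. The change is worth making because it corrects what can be concluded and needs no new data.

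**What to change.** In section 2.5:

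- State that stability will not be inferred from a non-significant test.
- For each unamended item rated in both final rounds, report, among experts who answered both, the change in percentage agreement with a paired 95% CI. Use a method valid for small numbers, such as a score interval; a Wald interval has zero width when nobody crosses.
- Report how many experts moved up and how many moved down across the agree line.
- Keep any Wilcoxon test in its paired (signed-rank) form and as descriptive only.
- If a stable label is wanted, set the largest tolerated change before round one and check that the rule can be met with 30 experts. A ±15-point CI rule is shown above only as an illustration; it would label few items stable even when nothing has truly changed.

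**Cost.** A few sentences and a simple calculation on responses that are already collected and must be linked by expert to show each participant their earlier answer. The real downside is that fewer items, or none, can be declared stable. The others would be reported as having stability not shown.

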### 2.3. Subject Enrollment

A purposive sample of individuals will be invited via email to participate in this Delphi study. An email invitation will be sent to the potential panelists and will include a Delphi study fact sheet to provide information about the study. Following agreement to participate, a participant demographic questionnaire will be issued to assess eligibility for the study. Prior to the round one questionnaire, participants will answer questions related to basic demographics (age, sex, country of residence, current institution, or clinic) along with professional credentials, experience related to clinical practice, relevant academic experience, and DN experience for headache management. Upon confirmation of interest and eligibility, a REDCap survey will be sent electronically to the participant for rounds one through three. The principal investigator will be responsible for executing and managing all aspects of the survey process through REDCap. For participants who are non-English speaking, a translated version of the invitation email, and surveys for the study will be provided. Following consent to participate, each panelist will be asked to commit to participation in each round of the Delphi. Experts will be informed that participation is completely voluntary and there are no consequences for withdrawing from the study at any time or refusing to participate. Participants will be provided with a Delphi study information fact sheet explaining the type of data being collected and the reason for carrying out such a study. Potential participants will be provided with a clear explanation of the anticipated process, and an explanation that participation would last a period of 3–4 months.

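### The Wilcoxon test planned for stability and consistency detects only a net shift in ratings, so a non-significant result does not show that experts kept their answers

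*Protocol article*

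**What the plan says.** Section 2.5 (Statistical Analysis) names one method for between-round stability: "Wilcoxon rank-sum tests will be used for the final round to evaluate stability and consistency of responses between the final two rounds". It gives no significance level, no rule for reading the result, and no measure of how far individual experts agree with their own earlier answers.

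The data are repeated ratings by the same people. Section 2.3 says "each panelist will be asked to commit to participation in each round of the Delphi", and section 2.2 says "We aim to recruit and retain 30 experts from multiple countries". Section 2.4.1 sets the scale: "Experts will rate their level of agreement for the included items using a 5-point Likert-scale".

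Change between rounds is part of the design. Section 2.4.3 says "In round three, participants can modify their answers from round two based on results and feedback from that round", and adds: "Participants will be able to see the amount of consensus on statements from the previous round, and where they answered compared to the group".

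Other measures sit beside the test. Section 2.5 says "Percentage agreement calculations will be the primary measure throughout all rounds of this Delphi study", and allows the IQR and median as optional replacements or additions.

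**The concern.** The test and the question do not match. Strictly, the rank-sum null is that the two rounds have equal distributions. Its statistic, however, compares only how often a rating from one round exceeds a rating from the other. The signed-rank statistic likewise weighs upward changes against downward ones. If experts move in opposite directions, or close in on a central answer from both sides, the movements offset and the statistic stays near its null value.

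The phrase stability and consistency of responses makes a different claim: that experts held their answers. A test used to evaluate stability will naturally be reported as supporting it when the result is non-significant. The published paper could then describe an item's ratings as stable when most of the panel had changed their minds. Readers would use that statement to judge how settled the expert opinion behind a recommendation is.

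**Working it through.** The article gives no figure for this test, so there is nothing to reproduce. The check asks what the test returns for items that the article's rules would send to round three unamended.

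**Inputs.** Panel n = 30 (section 2.2); 5-point scale (2.4.1), coded 1 = strongly disagree to 5 = strongly agree; consensus at 75% (2.4.1). Assumed, because not stated: two-sided alpha of 0.05, non-significance read as stable, and rounds two and three as the final two rounds.

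**Eligible items.** Consensus needs 0.75 × 30 = 22.5, so 23 experts. Sections 2.4.1 and 2.4.2 send items with 50% agreement or less (15 or fewer experts), or rated unsure overall, for amendment. Items re-rated with unchanged wording therefore start at 16 to 22 of 30 in agreement (53.3% to 73.3%).

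**Formulas.** U = (pairs with round three above round two) + ½ (tied pairs), over 30 × 30 = 900 pairs; null mean 450. With N = 60 and tie sizes t, Var(U) = (900/12) × [61 − Σ(t³ − t)/(60 × 59)]. Weighted kappa = 1 − (observed weighted disagreement)/(expected weighted disagreement), with quadratic weights.

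**Case A: trading sides at 66.7% agreement.** Round two has 10 experts at 2 and 20 at 4. Then k experts move from 2 to 4 and k others from 4 to 2.
- The counts are unchanged, so U = 450 and rank-sum p = 1.00 for every k.
- The k rises equal the k falls in size and number, so signed-rank p = 1.00 as well.
- Agreement (66.7%), median (4) and IQR (2) do not move.
- Only two categories are used, so the weights cancel. Observed disagreement is 2k/30; expected is 2 × (1/3) × (2/3) = 4/9. Kappa = 1 − (2k/30)/(4/9) = 1 − 0.15k.

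| k each way | Experts changing | p, both tests | Weighted kappa |
|---|---|---|---|
| 1 | 2 of 30 | 1.00 | 0.85 |
| 3 | 6 of 30 | 1.00 | 0.55 |
| 5 | 10 of 30 | 1.00 | 0.25 |
| 10 | 20 of 30 | 1.00 | -0.50 |

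**Case B: convergence on agree.** Counts in categories 1 to 5 go from 3/4/5/9/9 to 0/0/5/25/0. Agreement rises from 18/30 = 60% to 25/30 = 83.3%, crossing the threshold; the median is 4 both times; the IQR falls from 2 to 0.
- At most 5 + 9 = 14 experts can have kept their category, so at least 16 of 30 changed.
- Pairs above: 5 × 7 + 25 × 12 = 335. Ties: 5 × 5 + 25 × 9 = 250. U = 335 + 125 = 460.
- Tie sizes 3, 4, 10, 34, 9 give Σ(t³ − t) = 24 + 60 + 990 + 39,270 + 720 = 41,064. Var(U) = 75 × (61 − 11.6) = 3,705; SD 60.87.
- z = 10/60.87 = 0.164, p = 0.87.
- Signed-rank depends on who moved. If the 14 possible stayers all stay, p = 0.22; if experts keep their rank order (21 change), p = 0.15.

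**Case C: answers redrawn at random.** If each expert answers afresh in each round from 7/13/20/40/20% (60% agreement), the chance of a changed category is 1 − (0.0049 + 0.0169 + 0.04 + 0.16 + 0.04) = 73.8%. The two rounds share one distribution, so a valid test rejects at about its nominal level. A simulation of 10,000 panels gave 4.5% for both tests.

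**Where the test does respond.**
- One-sided movement to agree from 0/5/7/14/4: with 10 movers, rank-sum p = 0.035. With 5 movers (60% to 76.7%), rank-sum p = 0.39 and signed-rank p = 0.025.
- Lopsided polarisation, 0/0/10/20/0 to 10/0/0/0/20: U = 20 × 30 = 600, SD 64.8, z = 2.32, rank-sum p = 0.021. If the ten experts at unsure are the ones who drop to strongly disagree, signed-rank p = 0.63.

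**The case against.** The strongest reply is that little depends on this test. Retention, removal and further rounds follow percentage rules, percentage agreement is reported in every round, and the IQR may be. In case B those figures would show the change. The article also does not say that a non-significant result means stable. Whether stability is a group or an individual property is partly a matter of definition, and the article cites a source for its approach that is not at hand. All of this stands, and it limits the point to the wording and evidence of one reported statement. It does not remove the point, because case A leaves agreement, median and IQR untouched and nothing in the plan would show it.

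Three stronger readings are tempting and are not supported:

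- A reader might infer that the test misses any convergence or polarisation. It does not: lopsided forms can be flagged, as shown above. Striking examples centred on unsure, such as an even spread across all five categories collapsing to unsure, start at 50% agreement or less and would be amended before re-rating.
- A reader might infer that the test cannot show movement toward consensus. Consensus here is directional ("We define that consensus has been reached when 75% percent of participants" choose one of the two agreement categories), so one-sided movement toward it can be detected.
- A reader might infer that the list of consensus items is at risk. It is not.

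That rank-sum treats the two rounds as independent samples is a separate matter. Pairing gains power against net shift, but signed-rank has the same blind spot for offsetting changes.

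**Conclusion.** The point holds in a limited form. The named test does not answer the question section 2.5 sets for it. Among items eligible for unamended re-rating, up to 20 of 30 experts can trade sides at p = 1.00 on both Wilcoxon tests, and a 60% to 83.3% convergence in which at least 16 of 30 change gives a rank-sum p of 0.87. The blind spot covers offsetting switches and roughly balanced convergence or polarisation. The harm is confined to the published stability and consistency statement.

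This rests on the assumed alpha of 0.05, on a full panel of 30, and on non-significance being read as stability, which the article implies by the test's purpose but does not state. The cases are constructed to show what the test can miss; the documents give no basis for saying how often such patterns will occur.

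**What to change.** In section 2.5, base the stability and consistency statement on matched experts. For each item rated with the same wording in both final rounds, report:

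- the number of experts who rated it in both rounds and the percentage who changed category;
- the weighted kappa between rounds, with the weighting stated;
- the IQR in each round and its change, to show convergence or divergence.

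Keep a Wilcoxon test, in its paired form, only as a check for net shift, and say that a non-significant result will not be described as stability. Leave amended items out of the comparison.

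The cost is a few sentences and routine output from the same data. Responses must be linked across rounds by a de-identified code, but showing experts where they stood against the group already requires that link. The downside is a slightly longer results table, and some items will look less stable than under the present plan.
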